## Abstract

**Introduction:**

Adolescent idiopathic scoliosis (AIS) is a three-dimensional spinal deformity that can impair posture, function, and quality of life. Schroth exercise, a physiotherapeutic scoliosis-specific exercise, has demonstrated benefits in reducing Cobb angle and improving patient-reported outcomes. Traditional Chinese Medicine (TCM) manipulation may modulate musculoskeletal asymmetry and pain, potentially exerting synergistic effects when combined with Schroth therapy. This study aims to evaluate whether TCM manipulation plus Schroth exercise is superior to Schroth exercise alone in improving spinal curvature, patient-centered outcomes, and paraspinal symmetry in AIS.

**Methods:**

This is a single-center, randomized controlled, two-arm parallel-group superiority trial. Sixty adolescents (aged 10–18) with idiopathic scoliosis and Cobb angle 10°–45° will be randomized 1:1 to: (1) Schroth therapy alone (control) or (2) TCM manipulation combined with Schroth exercise (intervention). Primary outcome is change in Cobb angle measured by full-length standing anteroposterior spinal radiograph before and after the intervention. Secondary outcomes include Angle of Trunk Rotation (ATR), paraspinal thermal asymmetry assessed by infrared thermography, and health-related quality of life measured by the Scoliosis Research Society-22r (SRS-22r) questionnaire. Participants will be randomly allocated (1:1) using a computer-generated, stratified block randomization sequence with allocation concealed by sealed opaque envelopes. The analysis will follow the intention-to-treat (ITT) principle, and an ANCOVA adjusting for baseline measurements will be used for between-group comparisons. A total sample size of 60 participants (30 per group) was determined *a priori* to provide 80% power (*α* = 0.05, *β* = 0.20) to detect a clinically meaningful difference in Cobb angle, allowing for a 20% attrition rate.

**Discussion:**

If effective, the combined regimen could offer a non-invasive, integrative therapeutic option for AIS, with implications for conservative management guidelines.

**Ethics and dissemination:**

The study protocol was approved by the Ethics Committee of Yibin Traditional Chinese Medicine Hospital [Approval No. KY2024 Review (016)]. The trial has been prospectively registered in the International Traditional Medicine Clinical Trial Registry (ITMCTR) on January 6, 2025. The study will be conducted in accordance with the principles of the Declaration of Helsinki (Edinburgh 2000 revision). The trial findings will be disseminated through publication in peer-reviewed journals.

**Trial registration:**

The full trial protocol and statistical analysis plan can be accessed via the ITMCTR website (Registration No. ITMCTR2025000131). Any important modifications to the protocol will be submitted for approval by the institutional ethics committee and updated in the ITMCTR.

## Introduction

1

Adolescent idiopathic scoliosis (AIS) is a structural, lateral, three-dimensional spinal deformity with onset during growth spurts in adolescence (1). If left untreated, moderate curves can progress, leading to cosmetic concerns, back pain, and psychosocial impairment (2). Severe untreated curves may progress and result in cardiorespiratory compromise (3). Conservative management, especially for mild-to-moderate curves, aims to halt progression and improve function without surgery (4). Schroth therapy is a scoliosis-specific exercise program focusing on three-dimensional corrective postural training, breathing techniques, and sensorimotor re-education. Evidence from randomized controlled studies indicates that Schroth exercises can reduce Cobb angle and improve trunk symmetry and quality of life in AIS patients (5–7).

Complementary therapies, including manual modalities, have been explored to enhance conservative management. Recent integration of manual therapies with scoliosis-specific exercise has shown promise; for example, combinations of spinal manipulation with Schroth have been evaluated with preliminary favorable findings (8, 9). Similarly, in China, Traditional Chinese Medicine (TCM) manipulation therapies such as Tuina are commonly used as conservative interventions for scoliosis (10). This approach employs soft-tissue relaxation techniques and spinal joint adjustments to rebalance paraspinal musculature and improve spinal alignment (11). This may alleviate pain and contribute to better overall patient outcomes.

However, current evidence remains limited. Most existing studies investigating manual therapies for scoliosis are preliminary, with small sample sizes, heterogeneous interventions, and methodological shortcomings that restrict the generalizability of their findings (12). Therefore, this study is designed to test the hypothesis that combining TCM manipulation with the Schroth method will yield superior improvements in spinal curvature, postural control, and pain reduction compared with the Schroth therapy alone. This trial aims to provide rigorous clinical evidence for the integration of TCM manipulation into evidence-based conservative management of AIS.

## Materials and methods

2

### Study design

2.1

This is a single-center, two-arm, parallel-group, randomized controlled trial. The study is being conducted at Yibin Traditional Chinese Medicine Hospital in Sichuan Province, China. This hospital is a designated National Center for Scoliosis, ensuring an adequate pool of eligible participants to achieve the target sample size within the planned timeframe. The overall trial recruitment period spans from June 1, 2025, to December 31, 2025, following ethical approval (granted in 2024) and prospective trial registration (January 6, 2025). To facilitate recruitment, advertisements have been placed in prominent locations within the outpatient hall of Yibin Hospital of Traditional Chinese Medicine and disseminated through the hospital's official WeChat account. There was no direct involvement of patients or the public in the design, conduct, or reporting of this trial. Public involvement was limited to dissemination of recruitment advertisements through the hospital's official WeChat account and its redistribution by community members.

The sponsor, Yibin TCM Hospital, is responsible for study initiation and oversight. The sponsor provided input on study design and facilitates trial management. However, all data collection is being carried out, and all future data analysis and interpretation will be performed, by the research team independently. The funder (Yibin Science and Technology Department) had no role in the study design and will have no role in the conduct, analysis, or decision to publish this study.

The study protocol was developed in accordance with the SPIRIT 2025 statement (13) and will be reported following the CONSORT (Consolidated Standards of Reporting Trials) guidelines. A completed SPIRIT checklist is provided as Supplementary Material. For each individual participant, the study timeline is defined relative to the date of randomization (designated as Week 0). The schedule of enrollment, interventions, and assessments for each participant is detailed in Table 1, and participant flow will be documented using a CONSORT diagram (Figure 1).

**Table 1 T1:** Schedule of enrollment, interventions, and assessments (SPIRIT schedule).

		STUDY PERIOD				
		Enrollment	Allocation	Post allocation	Close-out	Follow-up
TIMEPOINT	Week	0	0	1	2	12
ENROLLMENT						
Inclusion/exclusion criteria		√				
Informed consent		√				
Medical history		√		√	√	
Random allocation			√			
INTERVENTIONS						
TCM Manipulation						
Schroth Therapy						
Home-based Schroth program						√
ASSESSMENTS						
x-Ray		√				√
ATR		√			√	
IR (*Δ*T)		√			√	√
SRS-22r		√			√	√
Adverse events				√		√
Safety evaluation					√	√

**Figure 1 F1:**
[figure not shown]
CONSORT flow diagram.

The Ethics Committee of Yibin Traditional Chinese Medicine Hospital has given the study approval [Approval No. KY2024 Review (016)]. The study has also been registered at the website of the International Traditional Medicine Clinical Trial Registry on January 6, 2025. The study will adhere to the tenets of the Declaration of Helsinki (Edinburgh 2000 revision).

### Participants

2.2

#### Inclusion criteria

2.2.1

Eligible participants who meet the following criteria will be included:(i) Diagnosed with AIS; (ii) Cobb angle between 10° and 45°; (iii) Age 10–18 years, any gender; (iv) Able to provide informed consent (parental/guardian consent where applicable) and comply with follow-up; (v) Able to undergo interventions, spinal radiography, and infrared thermography; (vi) Not currently in a scoliosis bracing program or requiring immediate bracing at the time of enrollment. (vii) No other concurrent scoliosis treatment during study period.

#### Exclusion criteria

2.2.2

Participants meeting any of the following criteria will be excluded: (i) Severe spinal deformity affecting cardiopulmonary function or requiring immediate surgical correction; (ii) Congenital spinal anomalies or other structural pathology (e.g., spondylolisthesis, tumor, tuberculosis, fracture) incompatible with loading/manipulation; (iii) Severe primary systemic diseases (cardiovascular, pulmonary, renal, hematologic, rheumatic, neuromuscular); (iv) Prior spinal corrective surgery or non-operative treatment within past 3 months; (v) Skin conditions preventing manual manipulation; (vi) significant psychiatric disorders or known poor compliance; (vii) Other conditions precluding participation or protocol adherence.

### Interventions

2.3

#### TCM manipulation and Schroth therapy

2.3.1

Participants in the intervention group will receive standardized TCM manipulation immediately before each supervised Schroth session during the initial 2-week inpatient phase. Both interventions will be delivered twice daily, five days per week: Schroth sessions will last approximately 2 h, and each TCM manipulation will last approximately 30 min. The TCM protocol is standardized to ensure reproducibility and delivered by licensed practitioners with over five years of clinical experience. Techniques target paraspinal soft tissues, acupoints along the Bladder Meridian, and spinal mobilization, aiming to reduce myofascial tension, enhance segmental mobility, and facilitate three-dimensional postural correction (Table 2, Figure 2).

**Table 2 T2:** TCM manipulation.

Step	Manipulation Technique	Procedure Description
1	*Gunfa* (Rolling) and *Zhang Roufa* (Palm Kneading)	Patient in prone position. Apply rolling and palm kneading to the muscles along the Bladder Meridian of the back and the *Jiaji* region, moving back and forth several times. Palpate for *jingbi* (tender/obstructed) points. Use *Roubo Fa* (kneading and plucking) to relax tense muscles; use rolling and palm kneading on soft or weak musculature. Duration: ∼10 min.
2	*Yizhichan Tuifa* (One-finger Zen Pushing) with *Zhi Roufa* (Finger Kneading)	Based on syndrome differentiation, select acupoints such as *Feishu* (BL13), *Xinshu* (BL15), *Ganshu* (BL18), *Pishu* (BL20), *Weishu* (BL21), *Shenshu* (BL23), *Dachangshu* (BL25). Push along the point using the one-finger Zen technique, pausing at each point for finger kneading 1–2 min, until a tolerable aching/distending sensation occurs. Duration: ∼5 min.
3	*Zhang Ca Fa* (Palm Rubbing) and *Niejifa* (Spinal Pinching)	Apply a small amount of Vaseline or similar medium along the *Du Mai* (Governor Vessel), *Jiaji*, and Bladder Meridian areas. Perform palm rubbing in straight, back-and-forth movements until the skin is slightly red and warm, then pinch along the spine for 3–5 passes.
4	Rhythmic Spinal Oscillation	Place one palm over the cervicothoracic junction or a selected spinal segment for stabilization, and the other palm on the lumbosacral midline. Using the spine as the axis, both palms work together to rhythmically oscillate the spine and pelvis, gradually increasing amplitude within patient tolerance.
5	Seated Rotational and Extension Stretch	Patient seated, arms crossed hugging a pillow, with lower limbs and pelvis stabilized. Practitioner stands behind and slightly to the side, placing one hand on the convex side of the curve for support and the other under the axilla to grasp the opposite shoulder. Guide the patient into slight forward flexion, then rotation and extension toward the same side. Repeat for the opposite side.
6	Bilateral Axillary Lift and Thoracic Distraction	Practitioner passes both arms under the patient's axillae, grasping the upper arms, and gently lifts upward and backward to distract and stretch the thoracic spine, producing mild joint loosening and widening of intervertebral spaces.
7	Finishing Technique	Conclude with gentle tapping or kneading to relax tissues. Total treatment duration: approximately 30–40 min per session.

**Figure 2 F2:**
[figure not shown]
TCM manipulation procedures. **(a)** Gunfa (rolling) and Zhang Roufa (palm kneading) are applied along the Bladder Meridian and the Jiaji region to relax paraspinal soft tissues. **(b)** Yizhichan Tuifa (one-finger Zen pushing) with Zhi Roufa (finger kneading) is performed on selected acupoints to induce a tolerable aching or distending sensation. **(c)** Zhang Ca Fa (palm rubbing) and Niejifa (spinal pinching) are applied along the Du Mai, Jiaji, and Bladder Meridian regions to warm the tissues and stimulate local circulation. **(d)** Rhythmic spinal oscillation is performed with both hands to mobilize spinal segments within the patient's tolerance. **(e)** A seated rotational and extension stretch is guided by the practitioner to promote three-dimensional spinal alignment. **(f)** A bilateral axillary lift with thoracic distraction is used to gently distract and open the thoracic spine. **(g)** The procedure concludes with gentle tapping or kneading to relax the tissues. A detailed step-by-step description of these procedures is provided in Table 2, and a full instructional video has been uploaded as Supplementary Material.

The intervention group has an additional ∼30 min of therapist contact per session due to the TCM manipulation. Both groups, however, receive the same number of sessions and equivalent follow-up phone support to promote adherence, to partly balance overall attention.

#### Schroth therapy alone

2.3.2

Participants in the control group will undergo Schroth therapy only. During the initial 2-week inpatient phase, they will receive twice-daily supervised Schroth sessions, five days per week, each lasting approximately 2 h, administered by certified Schroth therapists. This will be followed by a 10-week home-based Schroth program performed three times per week. The intervention includes individualized three-dimensional corrective exercises, sensorimotor training, postural education, and corrective breathing techniques, as summarized in Table 3.

**Table 3 T3:** Schroth therapy.

Step	Exercise Component	Procedure Description
1	Postural Awareness Training	Patient is guided to recognize their scoliosis curve pattern using mirrors and verbal cues. Education is provided on three-dimensional scoliosis correction principles (derotation, deflexion, elongation).
2	Corrective Breathing (Rotational Angular Breathing, RAB)	Patient performs segmental breathing into the concave side of the ribcage while maintaining corrective posture, emphasizing expansion of collapsed areas and active exhalation to promote rib derotation.
3	Pelvic Alignment and Stabilization	Exercises to correct pelvic tilt and rotation are performed in standing, sitting, or supine positions, using isometric activation of gluteal and abdominal muscles to stabilize the pelvis.
4	Spinal Elongation and Axial Stretching	Patient actively lengthens the spine against gravity (in seated or standing positions), with manual or elastic band assistance to increase vertebral spacing and reduce curve compression.
5	Asymmetric Strengthening	Targeted strengthening of trunk muscles on the convex side to support curve correction, using resistance bands or body weight.
6	Symmetric Integration Exercises	Functional activities performed in corrected posture (e.g., squatting, stepping, reaching), reinforcing muscle memory of the corrected alignment.
7	Relaxation and Recovery	Gentle stretching and breathing exercises to relax overactive musculature and prevent fatigue after corrective exercises.

Following discharge, participants will continue with a 10-week home-based Schroth program, performed three times per week under remote monitoring and guidance. To promote adherence, participants will receive weekly follow-up phone calls and are required to record each session in a structured exercise diary, which will be reviewed by the study team. No additional TCM manipulation will be provided during the home phase. Concomitant care such as routine daily activities and non-scoliosis–specific physical activity will be permitted. During the study period, participants will be instructed to avoid any other scoliosis-specific treatments, such as bracing, additional exercise programs, or non-study manual therapies.

#### Adverse events

2.3.3

Adverse events are defined as any untoward medical occurrence in a participant, and will be categorized by severity (mild/moderate/severe) and relatedness to the intervention. Serious adverse events (SAEs) are defined as events that are life-threatening, require/prolong hospitalization, or result in significant disability or harm.

Adverse events will be systematically assessed at each study visit. Participants will be specifically asked about musculoskeletal discomfort, skin reactions, and neurological symptoms. All adverse events will be recorded, graded, and reported to the ethics committee as per institutional policy. Serious adverse events will trigger immediate review. The trial may be terminated based on the findings of this review. Participants who experience trial-related adverse events will receive free emergency medical care by the investigators.

Additionally, disease progression will be closely monitored as a key safety parameter. All participants will be regularly assessed for clinical signs of worsening, such as increased Angle of Trunk Rotation (ATR) or observable postural changes. If significant clinical deterioration is suspected, a follow-up radiograph will be obtained to confirm progression. Upon confirmation of radiological or significant clinical worsening, the study protocol includes provisions to withdraw the patient from the trial and ensure they receive appropriate standard care.

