### Outcomes

2.6

To minimize radiographic exposure, outcome measures will be assessed at different timepoints based on their invasiveness and clinical practicality. All outcomes will be assessed at baseline (week 0) and study completion (week 12). Additionally, to capture the immediate effects of the intensive inpatient intervention, all secondary outcomes will also be assessed immediately following the 2-week intensive intervention period (week 2).

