#### Primary outcome

2.6.1

Change in the Cobb angle (degrees) of the major structural curve (defined as the curve with the largest Cobb angle), will be measured on full-length standing anteroposterior spine radiographs at weeks 0 and 12 only. A fixed tube-to-detector distance of 200 cm, with pelvic leveling blocks used if necessary to compensate for leg length discrepancy. All measurements will be performed by two independent readers blinded to participant allocation and time point. A consensus process with a third adjudicator is predefined for discrepancies greater than 3°. The intra- and inter-rater reliability of the measurements will be formally assessed using intraclass correlation coefficients (ICCs).

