### Data collection and monitoring

2.8

Designated outcome assessors, blinded to assignment, will record all measurements on case report forms (paper) and subsequently enter data into a secure electronic database (computerized CRFs). The Academic Committee of Yibin Traditional Chinese Medicine Hospital will function as the independent Data Monitoring Committee (DMC), supervising trial conduct and participant safety. The DMC is independent of the sponsor and the funder. No formal interim efficacy analysis is planned given the sample size. However, the DMC will conduct ongoing safety monitoring. In the event of any safety concerns or unexpected serious adverse events, the DMC is empowered to recommend trial modification or early termination. Data quality audits will be conducted monthly by independent monitors. The statistician performing the outcome analysis will remain blinded to group allocation until the primary analysis is complete. To promote participant retention, reminder phone calls and follow-up messages will be provided. For participants who discontinue or deviate from the intervention protocol, outcome data will continue to be collected at all scheduled time points whenever possible.

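### Section 2.3.3 takes confirmed progressors out of the trial while 2.8 keeps following those who stop treatment and 2.9 claims ITT, so the week-12 Cobb value may be lost because of the outcome itself

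*Protocol article*

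**What the plan says.** Section 2.3.3 (Adverse events) treats curve progression as a safety matter. It says "All participants will be regularly assessed for clinical signs of worsening", naming trunk rotation and visible posture as examples, and calls for an extra radiograph when deterioration is suspected. The trigger for action is worded "Upon confirmation of radiological or significant clinical worsening", with no threshold in degrees. The consequence of meeting that trigger is given as follows: "the study protocol includes provisions to withdraw the patient from the trial and ensure they receive appropriate standard care".

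Section 2.6.1 (Primary outcome) says the Cobb angle "will be measured on full-length standing anteroposterior spine radiographs at weeks 0 and 12 only". Section 2.6 adds a week-2 visit for the secondary outcomes only.

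Section 2.3.2 describes the home phase as "performed three times per week under remote monitoring and guidance" and says "participants will be instructed to avoid any other scoliosis-specific treatments, such as bracing".

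Section 2.8 (Data collection and monitoring) says: "For participants who discontinue or deviate from the intervention protocol, outcome data will continue to be collected at all scheduled time points whenever possible".

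Section 2.9 applies intention-to-treat to all analyses and compares change to week 12 by ANCOVA adjusted for baseline Cobb angle. It names full-information maximum likelihood for the mixed models and multiple imputation as a sensitivity analysis. The Discussion says that progressors can move to bracing or other care and does not mention leaving the trial.

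**The concern.** The two rules differ in what the participant leaves. Section 2.3.3 speaks of leaving the trial; 2.8 speaks of leaving the intervention. Neither refers to the other, so an investigator with a confirmed progressor at, say, week 6 has two instructions and no order of precedence.

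The conflict matters because of the trigger. Withdrawal follows from radiographic worsening, which is the primary outcome, or from clinical worsening, which tracks it. If the literal rule is followed, the missing week-12 values are those of the participants who did worst, and the remaining participants no longer give the comparison that was randomised. The maximum-likelihood provision is written for the mixed models, not for the primary ANCOVA. Multiple imputation under missing-at-random would have to predict the missing Cobb values from data that may not carry the worsening.

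**Working it through.** **1. The texts side by side**

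| Question | 2.3.3 | 2.8 | 2.9 | Discussion |
|---|---|---|---|---|
| What ends on confirmed progression? | Trial participation | Not addressed by name | Not addressed | Move to bracing or other care |
| Are outcomes still collected? | Silent | Yes, for those off or departing from the intervention, if possible | Implied by ITT | Silent |
| May the confirmatory film replace week 12? | Silent | Silent | Silent | Silent |

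A progressor sent to standard care stops study treatment and, if braced, departs from 2.3.2. Section 2.8 can therefore be read to cover this participant, but no sentence says that it does.

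**2. The plan's own figure**

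Section 2.7 gives effect size 0.81, two-sided α 0.05 and 80% power. The noncentral-t calculation gives 24.92, so 25 per group with power 0.801. This reproduces the stated 50. With all 30 per group evaluable, power is 0.870.

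**3. Illustration of the literal reading**

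From the protocol: effect size 0.81; difference about 4–5° (midpoint 4.5° used); 30 per arm. Hence SD = 4.5/0.81 = 5.56°.

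Assumed, because the article gives no figure: progression means a change of +5° or more; control mean change μ is 0 to −2°; the intervention mean is μ − 4.5; a share p of progressors is withdrawn before week 12.

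With a = (5 − mean)/SD, and m_low and m_high the mean changes below and above the threshold:

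kept mean = [m_low·Φ(a) + m_high·(1 − Φ(a))(1 − p)] / [Φ(a) + (1 − Φ(a))(1 − p)]

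lost per arm = 30·(1 − Φ(a))·p

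Example, μ = 0 and p = 0.50:
- Control: a = 0.90, Φ = 0.816, m_low = −1.81, m_high = 8.03. Kept mean = (−1.81×0.816 + 8.03×0.184×0.5)/(0.816 + 0.092) = −0.81. Lost: 30×0.184×0.5 = 2.76.
- Intervention: a = 9.5/5.56 = 1.71, Φ = 0.956, m_low = −5.04, m_high = 7.27. Kept mean = (−5.04×0.956 + 7.27×0.0436×0.5)/(0.956 + 0.022) = −4.76. Lost: 30×0.0436×0.5 = 0.65.
- Observed difference: 4.76 − 0.81 = 3.95°, which is 12% below 4.5°.

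| p | Difference, μ = 0 | Lost (control / intervention) | Difference, μ = −2 | Lost (control / intervention) |
|---|---|---|---|---|
| 0.10 | 4.40° | 0.55 / 0.13 | 4.42° | 0.31 / 0.06 |
| 0.25 | 4.24° | 1.38 / 0.33 | 4.31° | 0.78 / 0.14 |
| 0.50 | 3.95° | 2.76 / 0.65 | 4.10° | 1.56 / 0.29 |
| 1 (extreme) | 3.23° | 5.52 / 1.31 | 3.65° | 3.12 / 0.58 |

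For p from 0.10 to 0.50 the difference shrinks by about 2–12%, and about 0.4–3.4 of 60 participants are lost. With μ = −4° the difference is 4.25–4.45° over the same range of p.

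Simulated ANCOVA power (6,000 runs per setting, simulation error about one percentage point) is about 79–86% for p = 0.10–0.50, against 86–87% with no loss, and 68–76% at p = 1. With no treatment effect, the type I error at p = 0.50 and p = 1 stays near 5%.

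**4. If 2.8 governs**

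The week-12 film is still sought from progressors, and withdrawal for progression causes no bias of this kind.

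**The case against.** The strongest reply is that the article resolves the conflict itself. Section 2.8 is general, a progressor on standard care has discontinued the intervention in the ordinary sense, the Discussion describes a change of care and not a loss of follow-up, and 2.9 claims ITT. This reading is reasonable, and under it the bias disappears. It does, however, require leaving the trial to mean leaving the treatment, which nothing in the article says.

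A second reply is that 2.3.3 only summarises provisions that a fuller protocol may set out. That may be so, but the summary names the trial as the thing left, and this is a stated rule, not an omitted detail.

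A reader might infer that a progressor's Cobb information is gone for good. The article does not support that. Section 2.3.3 calls for a radiograph when deterioration is suspected, so such a participant would usually have an off-schedule film. Two limits remain: clinical worsening is a separate trigger, and no sentence admits the early film in place of week 12.

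A reader might also infer a large bias from the 3.23° in the extreme row, which lies below the 3.5° minimal important difference cited in 2.7. That row needs every progressor to be caught early, although the only scheduled secondary-outcome visit before week 12 is at week 2 and the home phase is remote. The model also counts measured changes as real. Section 2.7 puts measurement error at about 3°. If that is taken as the error SD of the change, the true-change SD is √(5.56² − 3²) = 4.68° and p = 0.50 gives 4.05–4.23°. If it is taken as the error SD of each film, the true-change SD is √(5.56² − 2×3²) = 3.59° and p = 0.50 gives 4.24–4.40°. Both ranges are for μ from 0 to −2°. A control mean of 0° also sits uneasily with the article's premise that Schroth exercise reduces the curve. All of this stands and points to a modest effect.

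**Conclusion.** The point holds as an unresolved conflict between stated rules. Section 2.3.3, taken at its word, would lose the week-12 Cobb value for a reason tied to the primary outcome; 2.8 and 2.9 point the other way.

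The documents do not show that progressors will in fact be dropped. If they are, the loss is about 2–12% of a 4.5° difference for 10–50% caught early. That range rests on the assumed 5° threshold, SD 5.56° and control mean of 0 to −2°, and on more progression in the control arm. If manipulation patients progressed more, the bias would run the other way and overstate the benefit. That case is not quantified here, and the article gives no progression rate by arm. The expected losses of 0.4–3.4 participants are within the 20% attrition allowance, and the calculation gives no ground for claiming an inflated false-positive rate. Severity: minor to moderate.

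**What to change.** In 2.3.3, replace withdrawal from the trial with withdrawal from study treatment and transfer to standard care. State that follow-up continues under 2.8, that the scheduled week-12 Cobb film is still sought, and that it is analysed in the randomised group whatever care followed. Where the week-12 film cannot be obtained, use the confirmatory film in the missing-data sensitivity analysis.

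The cost is a few sentences. Patient care does not change, and no film is added beyond those already foreseen. The drawback is that the ITT estimate then includes any effect of rescue care such as bracing, which may dilute a difference between arms. The change should be made before any affected participant passes week 12.
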